## **4.3. Analysis populations**

The primary analysis will be conducted according to the Intention-to-Treat (ITT) principle [24]. We define the ITT population as all CID participants who have signed informed consent and answered the FFQ (which will define the group allocation [the proxy for 'randomization'] of the participants in analogy to randomized trials) regardless of their adherence otherwise to the study protocol. A *per-protocol* population will be defined as those who adhered to the biological treatment during the observation period and have complete data used for the analyses at the end of the study, and no major protocol violations.

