### 5.3. Adherence and reasons for withdrawal

The number of patients adhering to the protocol, i.e., those who continued the biological treatment from baseline to the follow-up visit, will be accounted for in the flowchart. Likewise, the flowchart will also account for the number of patients deviating from the protocol, i.e., they did not initiate biologic treatment after all, they ended treatment due to either adverse events or lack of efficacy, or they withdrew their consent (fig. 1).

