### 6.1.2. Key secondary outcome measures

Predefined key secondary outcomes include changes in generic outcomes from baseline to follow-up (14-16 weeks after treatment initiation) consisting of both clinical and patient reported outcomes (PRO):

- Health-related quality of life (HRQoL): the physical component summary from the Short Form Health Survey (SF-12 PCS)
- HRQoL: the mental component summary measure from the SF-12 (SF-12 MCS)
- HRQoL: symptom burden (from the short health scale [SHS])
- HRQoL (Disability): functional status (SHS)
- HRQoL: disease-related burden (SHS)
- HRQoL: general well-being (SHS)
- Acute phase reactant (CRP)
- Physician global assessment (0-100 mm VAS)
- Patient global assessment (0-100 mm VAS)

In addition, however not specifically defined in the published protocol:

- The proportion of patients continuing the biologic treatment (yes/no) at week 14-16.

The 12-item SF-12 is a shorter form of the Short Form 36 (SF-36) which is widely used for measuring HRQoL and has a range of 0-100 (higher values indicate better health), mean of 50 and a standard deviation of 10. The SF-12 questionnaire comprises questions about physical and social functioning over the past 4 weeks. From the SF-12, two summary measures can be estimated; PCS and MCS [35].

The Short Health Scale (SHS) is a four-item questionnaire assessing the patient's subjective experience of how their disease influences four health dimensions: 1) symptom burden (severity of symptoms, 0 = none, 100 = worst thinkable), 2) functional status (impact on daily activities, 0 = none, 100 = severely impaired function), 3) disease-related burden (concern over illness, 0 = none, 100 = constantly) and 4) general well-being (0 = good, 100 = terrible) [36]. The four questions are graded from 0-100 and presented individually, where higher

scores indicate negative experience. The SHS has been validated as a measure for HRQoL for use in UC [36] and CD [37].

CRP: Blood samples as specified in the protocol were collected by a trained laboratory technician and handled according to set procedures. Results from analysis of blood samples will be limited to CRP (mg/L) in this study.

Physician global assessment and patient global assessment\* is assessed on 100 mm VAS.

\* Patient global assessment is not collected for PsO, CD and UC.

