### 6.3. Missing data

As previously stated (under section 4.3), the primary analyses will be based on the ITT population. Accordingly, participants will be followed up, assessed and analyzed as members of their initial dietary group, irrespective of their adherence to the planned course of treatment with biological agents and potential personal changes in dietary habits (i.e., independent of withdrawals and cross-over phenomena). Every effort will be made to minimize missing data (i.e. both baseline covariates [ $X$ 's] and outcome data [ $Y$ 's]). Loss to follow-up and missing data for various reasons is however difficult to avoid in pragmatic, real-world observational studies, from clinical practice.

We will apply the analysis framework suggested by White et al (2011) in which missing data related to the ITT approach depend on making plausible assumptions about the missingness of the data and including all participants in subsequent sensitivity analyses [24]:

**#1. Attempt to follow up all participants who signed informed consent**, even if they withdrew from allocated treatment or significantly modified their dietary habits (i.e., we contact all individuals unless they explicitly stated that they had withdrawn their consent).

**#2. Perform a main analysis of all observed data that are valid under a plausible assumption.** For our primary analyses we will assume that data is 'Missing At Random' (MAR). The MAR assumption requires that, conditional on the observed data for the case,  $Y_{obs}$ , the probability that a value is missing does not depend on the true values of the missing items,  $Y_{mis}$ . Multiple imputation (MI) will be used to account for participants from whom we have an answered FFQ (i.e. the ITT population) but potentially with missing outcome information at follow-up.

**#3. Perform sensitivity analyses.** In order to explore the effect of departures from the assumption made in the main analysis (#2) other analysis techniques will be applied; these models will potentially be informative even if data are 'Missing Not At Random' [MNAR].

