**Use and reporting of analyses using multiple imputation.** When we assume data are missing at random (MAR), then unbiased and statistically more powerful analyses is possible by building a more general model based on multiple imputation. Multiple imputation (MI) is a general approach to the problem of missing data that allow for the uncertainty about the missing data by creating several different plausible imputed data sets and appropriately combining results obtained from each of them.

The MI first stage will be to create multiple (i.e. at least 5) copies of the dataset, with the missing values replaced by imputed values. These will be sampled from their predictive distribution based on the observed data.

The MI second stage will be to use standard statistical methods to fit the logistic regression model of interest to each of the imputed datasets; variables included in the imputation models will be listed. At least five imputed datasets will be created. Estimated associations (i.e.  $\ln[OR_i]$ ) in each of the imputed datasets will differ

because of the variation introduced in the imputation of the missing values, and they are only useful when averaged together to give overall estimated associations. Standard errors will be calculated using Rubin's rules [51] which take account of the variability in results between the imputed datasets, reflecting the uncertainty associated with the missing values. Valid inferences are obtained because we will be averaging over the distribution of the missing data given the observed data.

We will report the number of missing values for each variable of interest, and the number of cases with complete data for each important component of the analysis. We will provide reasons for missing values if possible and indicate how many individuals were excluded because of missing data when reporting the flow of participants through the study (Figure 1). We will provide explicit reasons for missing data for the primary outcome measure in terms of other variables and explore whether there are differences between individuals with complete and incomplete primary outcome data, by performing logistic regression analyses with "missingness" being the dependent variable ( $Y_{\text{Mis}}$  vs.  $Y_{\text{Obs}}$ ) and various baseline characteristics (covariates) as independent variables.

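### Section 6.3 imputes every missing week 14-16 outcome under MAR whatever the reason, so unassessed patients recorded as stopping the biologic for lack of efficacy can be imputed as responders

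*SAP*

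**What the plan says.** The primary analysis uses the ITT population, which section 4.3 defines as everyone who consented and answered the food frequency questionnaire, "regardless of their adherence otherwise to the study protocol". Section 6.3 analyses them in their dietary group "irrespective of their adherence to the planned course of treatment with biological agents".

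Section 6.3 then sets the missing-data rule: "For our primary analyses we will assume that data is 'Missing At Random' (MAR"), and "Multiple imputation (MI) will be used to account for participants from whom we have an answered FFQ" when the follow-up outcome is missing. On the imputed values it says: "These will be sampled from their predictive distribution based on the observed data". No reason for missingness is treated differently.

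The plan does hold information on why patients stop. Under section 5.3 the flowchart separates out those who did not adhere because "they ended treatment due to either adverse events or lack of efficacy, or they withdrew their consent". Section 6.1.2 adds a key secondary outcome: "The proportion of patients continuing the biologic treatment (yes/no) at week 14-16".

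The primary endpoint in section 6.1.1 is clinical response to therapy at week 14-16. It is judged only by the disease-specific index, with no rule for patients who have stopped. Non-responder imputation appears only in section 6.4, as a sensitivity analysis.

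**The concern.** A patient whose recorded reason for stopping is lack of efficacy, and who then has no week 14-16 assessment, is not missing in an uninformative way. The recorded reason bears directly on whether the patient responded to therapy. Section 6.3 does not use it. Each such patient is given a response probability learned from patients who were assessed, most of whom presumably stayed on drug.

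Two things are at stake. The stated response proportions rise in any group that contains such patients. The odds ratio between diet groups can also move, in either direction, depending on how these dropouts split by diet.

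The other planned analyses give limited protection. Complete-case analysis drops these patients. The per-protocol population requires adherence to the biologic and complete data, so it excludes them too. The unmodified-eligibility analysis changes the population and states no different missing-data rule. Non-responder imputation does count them as failures, but does the same to everyone missing for unrelated reasons. Best and worst cases are described in the text of 6.4 but are absent from its numbered list and from Appendix Table 2. No planned analysis separates missing outcomes by reason. Section 6.4 reads agreement among the sensitivity analyses as added confidence, although several of them would agree because they share this omission.

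**Working it through.** **Inputs from the SAP.** Section 3.2 gives response of 60% (high fiber, low meat; HFLM) and 40% (the rest; LFHM), total N 318, allocation 1 to 2 (106 and 212), two-sided alpha 0.05 and power 0.924.

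**Assumed input.** d is the share of a group that stops for lack of efficacy, is not assessed, and is truly a non-responder. The SAP gives no figure. I use 5% to 15% per group, written HFLM/LFHM.

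**1. The plan's own figure.**
- Pooled proportion: (0.6 × 106 + 0.4 × 212)/318 = 0.4667.
- Standard error under the null: √[0.4667 × 0.5333 × (1/106 + 1/212)] = 0.0593.
- Standard error under the alternative: √[0.24 × (1/106 + 1/212)] = 0.0583.
- Power: Φ[(0.20 − 1.96 × 0.0593)/0.0583] = Φ(1.436) = 0.9245, which reproduces 0.924.
- Reference odds ratio: (0.6/0.4)/(0.4/0.6) = 2.25.

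**2. Worst case: imputation on diet group alone.** The imputed group rate equals the rate among assessed patients, p/(1 − d), and its odds are p/(1 − d − p). Scoring the same patients as non-responders returns p.

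| d, HFLM/LFHM | HFLM rate | LFHM rate | OR |
|---|---|---|---|
| 0/0 | 60.0% | 40.0% | 2.25 |
| 5%/5% | 0.60/0.95 = 63.2% | 0.40/0.95 = 42.1% | 2.36 |
| 10%/10% | 0.60/0.90 = 66.7% | 0.40/0.90 = 44.4% | 2.50 |
| 5%/15% | 63.2% | 0.40/0.85 = 47.1% | 1.93 |
| 15%/5% | 0.60/0.85 = 70.6% | 42.1% | 3.30 |

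At 10%/10%, 10.6 + 21.2, or about 32 of 318 patients, are affected. Of these, 10.6 × 0.667 + 21.2 × 0.444 = 16.5 are drawn as responders in an average imputed data set.

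**3. No true effect (50% in both groups).** Equal dropout gives equal imputed rates and OR 1.00, so no bias. With 5%/15% the rates are 0.50/0.95 = 52.6% and 0.50/0.85 = 58.8%, and OR = 1.111/1.429 = 0.78.

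**4. Continuation status in the imputation model.** Suppose stoppers are imputed with response probability q of 10% to 20% (assumed). The group rate becomes p + dq.
- 60% vs 40%, 5%/15%: q = 10% gives 60.5% vs 41.5%, OR 2.16; q = 20% gives 61% vs 43%, OR 2.07.
- 60% vs 40%, 15%/5%: 61.5% vs 40.5%, OR 2.35; 63% vs 41%, OR 2.45.
- 50% vs 50%, 5%/15%: 50.5% vs 51.5%, OR 0.96; 51% vs 53%, OR 0.92.

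Most of the distortion goes, but some remains because q is not zero.

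**The case against.** The strongest reply is that these patients' outcome is not known. Section 6.1.1 defines response by an index at week 14-16, and section 6.3 follows patients irrespective of adherence. Someone who stopped could still meet, say, the Crohn's disease index threshold at that visit. A reader might infer that the plan turns known treatment failures into responders. The SAP does not support that wording, since no clause makes stopping a non-response. Very likely non-response is as far as the document goes.

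Second, the imputation rules in 6.3 call for variables associated with the outcome and variables that predict missingness. Continuation status is collected and fits both. If it enters the model, the figures in step 4 apply rather than those in step 2. This stands as a limit on size. But the rules name neither continuation nor reason for stopping, and the planned regression of missingness uses baseline characteristics only. How well the model could learn a low probability depends on how many stoppers are assessed, which the SAP does not say.

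Third, 6.3 commits to following up all consenting participants, and 6.4 plans analyses for departures from MAR. Both help, but the first only reduces the number affected and the second leaves the primary estimate unchanged.

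Fourth, a reader might infer that the headline odds ratio is certainly biased. It is not: with no true effect and equal dropout there is no bias, and the largest shifts need a threefold difference in dropout by diet, which nothing in the SAP suggests.

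Finally, scoring only unassessed stoppers as non-responders means that an assessed stopper who meets the index still counts as a responder. That asymmetry is real. It follows from letting observed data take precedence, and the SAP should say so.

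**Conclusion.** The point holds in this form: followed as written, 6.3 allows patients recorded as stopping for lack of efficacy, and not assessed, to be imputed as responders to therapy in the primary analysis. The text establishes the mechanism but not its size, because no stopping or missingness rate is given. If imputation uses diet group alone, the assumed dropout splits move an OR of 2.25 to between 1.93 and 3.30, and equal dropout of 5% to 10% moves it to between 2.36 and 2.50. If continuation is in the model and stoppers get a 10% to 20% response probability, the 5%/15% case gives about 2.07 to 2.16. All these figures assume that the affected patients are true non-responders. The plan should be changed, since it already records the information needed to do better than a blanket MAR assumption.

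**What to change.** In section 6.3, for the primary analysis:

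- Before imputation, set clinical response to no for ITT patients who started therapy, have no week 14-16 outcome, and have lack of efficacy recorded as the reason for stopping.
- Leave every observed outcome as it is, including those of patients who stopped.
- Multiply impute the other missing outcomes, naming continuation status and reason for stopping as predictors in the imputation model.
- Keep the present all-MAR analysis as a sensitivity analysis, and add it to the list in 6.4 and to Appendix Table 2.
- State explicitly that unassessed stopping for lack of efficacy is scored as non-response to therapy. This is a choice about what the endpoint means and should be visible as one.

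The cost is SAP wording and one derivation step. Section 5.3 already requires the reasons for stopping for the flowchart; the rule applies only where lack of efficacy is actually recorded. The stated response rates will be slightly lower.

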### 3.2. Sample size and power considerations

Deciding on sample size is a well-known difficulty with exploratory prognostic factor research studies. To obtain an adequate number of outcome events, we applied 'the rule of thumb', whereby 10 outcomes are needed for

each independent variable. We planned to enroll 320 patients in total with the anticipation that 50% of these would experience a clinical response within the 14–16 weeks period after initiation of biological therapy. With this in mind and anticipating that we would observe at least 160 events (i.e., clinical response among the 320 patients), the study would be sufficiently powered to explore the impact of as many as 16 independent variables including condition and clinical center. Since using the ‘rule of thumb’ method to justify sample size is a debated practice, we went one step further and estimated the statistical power to detect differences between two dietary groups. For the contrast between groups and for a comparison of two independent binomial proportions (those with high-fiber, low-meat intake vs. other) using Pearson’s  $\chi^2$  statistic, with a  $\chi^2$  approximation, with a two-sided significance level of 0.05 ( $P < 0.05$ ), a total sample size of 318—assuming an ‘allocation ratio’ of 1 to 2 (one-third)—has an approximate power of 0.924 (i.e., >90% statistical power) if the anticipated proportions responding to therapy are 60% and 40%, respectively. However, due to pre-specified time constraints, inclusion to BELIEVE was terminated on 03-30-2020 before reaching the planned sample size of 320 patients in total.

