## 6.4. Sensitivity analyses

Where complete cases and multiple imputation analyses give different results, the analyst should attempt to understand why, and this should be reported in publications [52]. Robustness is a concept that refers to the sensitivity of the overall conclusions to various limitations of the data, assumptions, and analytic approaches to data analysis. Robustness implies that the treatment effect and primary conclusions of the trial are not

substantially affected when analyses are carried out based on alternative assumptions or analytic approaches. For the purpose of sensitivity, multiple sensitivity analyses will be performed to assess the robustness of the primary analyses. For instance, a simplistic 'single step, null responder imputation' would represent a conservative base case and is potentially valid even if data is 'missing not at random' as it assumes and implies that patients have not improved or worsened after entering the study. When there are missing outcome data for our dichotomous outcomes we will explore "best" and "worst" case scenarios by replacing missing values with "good" outcomes in one group and "bad" outcomes in the other group. Sensitivity analyses will include analyses based on:

- 1) complete case analysis,
- 2) a 'non-responder-imputation',
- 3) the 'per protocol population',
- 4) the population meeting the unmodified eligibility criteria  
(exclusion of patients initiating treatment with biologics targeting other agents than TNF and patients previously treated with biologics).

Results of the sensitivity analyses are presented in the Appendix, table 2. When the different sensitivity analyses are in agreement, and the analyses on the sensitivity analyses and the main analysis lead to essentially the same conclusions, confidence in the trial results is increased.

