Appendix Table 2. Sensitivity analyses of the comparison of HFLM versus LFHM.

| Outcome                                                                                                                                                                                                                                                                                                                                                                                                                                                                                                                                                | Complete-case analysis |      |                     | Non-responder imputation analyses |                     |          | Per protocol population |          |                     | Unmodified eligibility criteria |                     |          |
|--------------------------------------------------------------------------------------------------------------------------------------------------------------------------------------------------------------------------------------------------------------------------------------------------------------------------------------------------------------------------------------------------------------------------------------------------------------------------------------------------------------------------------------------------------|------------------------|------|---------------------|-----------------------------------|---------------------|----------|-------------------------|----------|---------------------|---------------------------------|---------------------|----------|
|                                                                                                                                                                                                                                                                                                                                                                                                                                                                                                                                                        | HFLM                   | LFHM | Difference (95% CI) | P value*                          | Difference (95% CI) | P value* | Difference (95% CI)     | P value* | Difference (95% CI) | P value*                        | Difference (95% CI) | P value* |

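### Of the four listed sensitivity analyses only non-responder imputation departs from missing at random, so agreement among the others is not evidence of robustness to that assumption

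*SAP*

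**What the plan says.** - **Main analysis.** SAP section 6.3, step #2, uses multiple imputation (MI) under MAR for participants who answered the food questionnaire but lack follow-up outcomes. The variable-selection rules later in 6.3 bring in correlates of the outcome and predictors of missingness, whether or not they are in the analysis model. The default is M=5.
- **Purpose of the sensitivity analyses.** Step #3: "In order to explore the effect of departures from the assumption made in the main analysis (#2) other analysis techniques will be applied". These are said to be potentially informative even if data are missing not at random (MNAR).
- **What is listed.** Section 6.4 numbers four: "complete case analysis", non-responder imputation (NRI), the per-protocol population, and the population meeting the unmodified eligibility criteria. Appendix Table 2 has these four blocks, beginning with "Complete-case analysis". Section 4.3 requires per-protocol participants to "have complete data used for the analyses at the end of the study".
- **What is in the text only.** Section 6.4 also plans best- and worst-case replacement of missing binary outcomes. Neither the numbered list nor Appendix Table 2 contains it.
- **How agreement is read.** Section 6.4 ends with a sentence beginning "When the different sensitivity analyses are in agreement". If they also match the main analysis, confidence in the results is said to rise. The sentence does not separate analyses by the assumption each one tests.

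**The concern.** A sensitivity analysis tests MAR only if it replaces MAR with something else. Complete-case regression keeps the assumption that missingness is ignorable given the model covariates. The per-protocol set is itself a complete-data set. The eligibility subset answers a question about population. That leaves NRI, a single fixed assumption, as the only listed analysis that bears on step #3.

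At stake is the robustness statement in the publication. Diet group is known for everyone in the ITT set by definition, so the missing item is chiefly the outcome. Complete case and MI then tend to carry the same MNAR bias. Under some patterns NRI is biased the same way, and all three can point towards the study hypothesis when diet has no effect. A reader told that the analyses agree would take this as reassurance about missing data that it does not give.

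**Working it through.** **1. Planning figure and the response rate used below.** Section 3.2 gives "a total sample size of 318", a ratio "of 1 to 2 (one-third", 60% versus 40% response, and a test "with a two-sided significance level of 0.05", hence 106 versus 212.

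- Pooled response = (106×0.6 + 212×0.4)/318 = 0.467.
- SE under the null = √(0.4667×0.5333×(1/106+1/212)) = 0.0593; under the alternative = √(0.24×(1/106+1/212)) = 0.0583.
- Power = Φ((0.20 − 1.96×0.0593)/0.0583) = Φ(1.436) = 0.924, as stated.

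The planning figure is not in dispute. It supplies 46.7% as a common response rate for a null example.

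**2. What each analysis assumes about missing outcomes.**

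| Analysis | Missing-data assumption |
|---|---|
| Main MI | MAR given the imputation model |
| Complete case | Ignorable given the analysis covariates |
| Per protocol | Complete data required; MAR not relaxed |
| Unmodified eligibility | Unchanged; population differs |
| NRI | Every missing outcome is a non-response |
| Best/worst case (text only) | Opposite extremes by diet group |

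**3. Expected values under a true odds ratio (OR) of 1.** Assumed rates: 35% missing among responders in the low-fibre/high-meat group (LFHM), 15% among everyone else. HFLM is the high-fibre/low-meat group.

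- HFLM: observed responders 0.467×0.85 = 0.397; observed non-responders 0.533×0.85 = 0.453; missing 0.150.
- LFHM: observed responders 0.467×0.65 = 0.304; observed non-responders 0.453; missing 0.243.
- Overall missing = (0.150 + 2×0.243)/3 = 21%.
- Complete case: observed LFHM response 0.304/(0.304+0.453) = 0.401 against 0.467; OR = 0.85/0.65 = **1.31**. MI with the same covariates targets the same value.
- NRI: 0.397 against 0.304; OR = **1.51**.
- Best case for HFLM: 0.547 against 0.304; OR = **2.77**. Worst case: 0.397 against 0.547; OR = **0.55**.

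With 40% and 10% instead, complete case is 0.9/0.6 = 1.50, NRI 1.86, best 2.79, worst 0.67.

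**4. When the bias arises.** Without covariates, complete-case OR = true OR × [(1−m₁)/(1−m₀)] in HFLM ÷ [(1−m₁)/(1−m₀)] in LFHM, where m₁ and m₀ are the missing fractions in responders and non-responders. If these are the same in both groups (35%/15% in each), the factor is 1. Bias needs missingness that depends on outcome differently by diet.

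**5. Simulation** (400 datasets, N=318, true OR 1.0, M=5, Rubin's rules; missingness rates and auxiliary strength assumed). MNAR pattern: HFLM 5% missing in responders and 35% in non-responders, LFHM 20% in both.

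| Setting | Complete case | MI | NRI | Same verdict, complete case and MI |
|---|---|---|---|---|
| MNAR, no auxiliary | 1.47 | 1.47 | 1.36 | 92% |
| MNAR, strong auxiliary imputed from | 1.48 | 1.28 | 1.38 | 85% |
| MAR given a strong auxiliary, imputed from | 1.60 | 1.02 | 1.16 | 66% |
| Same, auxiliary left out | 1.57 | 1.57 | 1.15 | 92% |

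In the first row complete case, MI and NRI were all significant in 17.7% of datasets; in the second, in 14.0%. Rows 1 and 4 show agreement while MI is biased; row 3 shows disagreement while MI is right. Comparing complete case with MI therefore tests the auxiliaries, not MAR.

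**6. Why best/worst case alone is not enough.** Take the plan's own effect (60% versus 40%, OR 2.25) with 20% missing completely at random in each group. The worst case is (0.48/0.52)/(0.52/0.48) = 0.85, so the bounds cross 1 with no departure from MAR at all.

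**7. Size of a graded departure.** In the example of step 3 the log-odds of response differ between missing and observed LFHM patients by ln[(0.35/0.15)/(0.65/0.85)] = ln 3.05 = 1.1. With 40%/10% the shift is ln 6 = 1.8. The HFLM shift is 0 in both.

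**The case against.** Several points on the other side stand.

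- A reader might infer that complete case must reproduce MI. The SAP does not support that: its selection rules call for auxiliaries from outside the analysis model, and a strong one driving missingness separates the two (1.60 versus 1.02). Missing baseline covariates, which 6.3 anticipates, are another route to divergence.
- A reader might infer that the SAP offers complete case as its MNAR check. It does not. Section 6.4 gives that role to null-responder imputation, and it asks the analyst to explain differences between complete case and MI, which is close to the right use.
- A reader might infer a rule that certifies the result. The SAP says only that confidence increases, and its condition covers all the sensitivity analyses. Best/worst case, if counted, would break agreement: in 20,000 unadjusted null datasets per scenario (35%/15% and 40%/10%), complete case, NRI and worst case were all significant in favour of HFLM in 0.01% or fewer.
- The per-protocol and eligibility analyses have legitimate purposes of their own, and robustness in 6.4 is defined more widely than missing data.
- The bias needs diet-differential, outcome-dependent missingness, and nothing in the SAP suggests that this occurred.

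None of this makes complete case, per protocol or the eligibility subset a departure from MAR. Nor does it place best/worst case in the list or table on which the agreement sentence will in practice be read.

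**Conclusion.** The point holds in a limited form. Step #3 of section 6.3 promises analyses of departures from MAR, and of the four listed only NRI is one. Unless strong auxiliaries drive missingness, complete case and MI give nearly the same log OR and share any MNAR bias; whether they agree or not, the comparison does not test MAR.

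Under assumed diet-differential missingness of about 21% overall and no true effect, complete case is about 1.31 and NRI about 1.51, in the same direction. Section 6.4 as worded would count that as support. These sizes illustrate what can happen; they do not predict what the data will show, because the SAP states no missingness rates. The primary analysis is unaffected. The defect lies in how the sensitivity results are labelled, tabulated and read, with nothing graded between MAR, one fixed imputation and the extreme bounds.

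**What to change.** 1. In 6.3 #3 and 6.4, describe complete case as a check on the imputation model. State that its agreement with MI, and that of the per-protocol and eligibility analyses, is not counted as robustness to MNAR.
2. Add best and worst case to the numbered list in 6.4 and to Appendix Table 2.
3. For the primary outcome, add a delta-adjusted MI: the same imputation model and analysis models, with the imputed log-odds of response shifted separately in HFLM and LFHM over a pre-stated range. A range of −2 to +2 would cover the shifts of 1.1 and 1.8 above, but it is an illustrative choice for the study team to justify. The pair (0, 0) reproduces the main analysis. Report the pairs at which the conclusion changes.
4. Base the MNAR robustness statement on NRI, best/worst case and the delta-adjusted analysis only.

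Cost: SAP wording and further runs of existing imputation code, with no new data. The downside is extra columns to report and possibly a less favourable robustness statement.
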